# Analgesic efficacy and safety of nalbuphine versus morphine for perioperative tumor ablation: a randomized, controlled, multicenter trial

**DOI:** 10.1186/s13063-022-06825-5

**Published:** 2022-10-22

**Keywords:** Tumor ablation, Perioperative, Pain, Nalbuphine

## Abstract

**Background:**

The study will compare the efficacy and safety of nalbuphine hydrochloride injection and morphine hydrochloride injection for perioperative analgesia in tumor ablation and the differences between the two groups regarding duration of surgery, average daily dose, patient satisfaction with analgesia, quality of life, and other indicators. Furthermore, it will evaluate the clinical application of nalbuphine and morphine for perioperative analgesia in ablation surgery and provides important reference and guidance for clinical practice.

**Methods:**

This is a randomized controlled study. Patients who were diagnosed by clinicians and required tumor ablation are enrolled and randomized to the experimental groups. In the test group, nalbuphine 80 mg + 0.9% normal saline (72 ml) is set in the patient-controlled analgesia pump, which is connected 15 min before ablation under electrocardiogram monitoring and surgery is performed immediately. The doses are as follows: initial,: 0.15 ml/kg,; background:, 0.5 ml/h,; compression:, 2 ml,; and lockout time:, 15 min. If the numeric rating scale is ≥ 4 points, the drug is administered by compression. The control group receives similar treatment under similar conditions as the test group except morphine (80 mg) is administered instead of nalbuphine (80 mg). The primary endpoints are the effective rate of analgesia and the incidence of adverse reactions (nausea and vomiting, dizziness, itching, constipation, hypoxemia, and urinary retention); the secondary endpoints are pain intensity, satisfaction with analgesia, duration of surgery, postoperative hospital stay, average daily dose, uninterrupted completion rate of surgery without complaints of pain, quality of life assessment, and vital signs.

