### Outcomes {12}

#### Main study outcome

Analgesic effective rate: Analgesic effective rate = number of patients with effective analgesia/total number of cases × 100%. NRS score (at rest) ≤ 3 points at all assessment time points is considered as effective analgesia and assessed at 1 min and 5 min after ablation, at the end of the surgery, and at 2 h, 6 h, 12 h, 24 h, and 48 h after surgery. The NRS is used for assessment, which consists of 11 numbers with the same interval from 0 to 10, with 0 representing “no pain” and 10 representing “most intense pain.” Patients are asked to choose one number to represent the pain intensity score.

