### Sample size {14}

The sample size and case allocation included patients who underwent tumor ablation. NRS score (at rest) ≤ 3 points during operation and within 48 h after the operation was defined as effective. Assuming that the effective rate was 90% in the nalbuphine group and 90% in the morphine group, the clinical cut-off value for non-inferiority between the two groups was 10% if the nalbuphine group is non-inferior to the morphine group, setting one-sided α-error level = 0.025, *β* = 0.2 (power = 0.8), and the sample size ratio of the two groups 1:1. Overall, 142 patients were required for each group calculated using the PASS15.0 software, and a total of 284 patients were required for the two groups. Based on the dropout rate of 10% (284 ÷ 0.9 = 316), a total of approximately 316 patients were planned to be included.

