#### Statistical analysis method

The number of included and completed cases in the overall and each site is listed in the case analysis, and three analysis datasets (FAS, PPS, and SS) are generated. Dropouts and excluded cases along with the reasons for their dropping out and exclusion are listed.Demographic and baseline data analysis: Descriptive statistics of demographic data and other baseline characteristic values: For continuous variables, total number of cases, mean, standard deviation, median, and minimum and maximum values are calculated. The t-test will be used for normally-distributed data and the rank-sum test will be used for data with skewed distribution. Frequency and proportion are calculated for countable and grade data. The chi-square test will be used for disordered classification data, and the rank-sum test will be used for ordinal data. Inferential statistical results (*P*-values) are presented based on descriptive statistics.Efficacy analysis:A.Analysis of the primary efficacy indicators (overall response rate): The overall response rate is compared using the chi-square test, corrected chi-square test, or exact probability test. The 95% confidence interval of the difference in response rates between the two groups will be calculated, and if the lower limit of the confidence interval is greater than −10%, the result will be considered non-inferior.B.Analysis of the secondary efficacy indicators: Differences in the scores of NRS at each time point and the total score between the two groups are compared by the *t*-test or rank-sum test; differences in the physician satisfaction VAS score and the nurse satisfaction VAS score between the groups are compared by the t-test or rank-sum test; the difference between the two groups regarding willingness to undergo ablation surgery another time will be compared by the chi-square test, corrected chi-square test, or exact probability test; differences between the two groups with respect to duration of surgery, postoperative hospital stay, and average daily dose will be compared by the t-test or rank-sum test; the difference in the uninterrupted completion rate of surgery without complaints of pain between the groups will be compared by the chi-square test, corrected chi-square test, or exact probability test.Safety analysis: The incidence of adverse reactions will be calculated, their frequency and proportion were systematically listed, and the percentage calculated. A detailed list of cases of various adverse events (AEs), the number and rate of cases, conversion of physical examination indicators, ECG, respiratory and circulatory indicators, and laboratory indicators that “turn normal to abnormal” or “intensify abnormal” after the test, and list clinical explanations will be recorded.

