### Adverse event reporting and harms {22}

#### Primary safety indicators

Incidence of common adverse reactions to opioid drugs, such as nausea, vomiting, vertigo, constipation, itching, urinary retention, hypoxemia, respiratory depression, drowsiness, delirium, and myoclonus are recorded. AEs are graded 1–5 according to the Common Terminology Criteria for Adverse Events 5.0 (CTCAE 5.0) of the National Cancer Institute (NCI).Grade 1: mild: asymptomatic or mild, clinical or diagnostic findings, no treatment required;Grade 2: moderate: minimal, local, or non-invasive treatment required, limiting age-appropriate instrumental activities of daily living;Grade 3: serious or medically significant but not immediately life-threatening, hospitalization or prolongation of hospitalization indicated, disabling, limiting self-care activities of daily living;Grade 4: life-threatening, urgent treatment required; andGrade 5: death related to AE.

If an AE is not listed in the NCI toxicity grading scale, it can be judged according to the following criteria:Grade I (mild): uncomfortable feeling, but does not affect normal daily activities;Grade II (moderate): uncomfortable degree enough to reduce or affect normal daily activities;Grade III (severe): unable to work or do normal daily activities; andGrade IV (fatal): disabling or fatal.

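### Adverse-reaction incidence is called a primary endpoint, but the Outcomes section, sample size, success rule and between-arm analysis cover only the analgesic effective rate

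*Protocol article*

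**What the plan says.** The Methods part of the abstract names two primaries: "The primary endpoints are the effective rate of analgesia and the incidence of adverse reactions". It then lists nausea and vomiting, dizziness, itching, constipation, hypoxemia and urinary retention. The two arm descriptions under Intervention description {11a} carry the same six.

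The body of the article differs:

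- **Outcomes {12}, Main study outcome:** one outcome only, "Analgesic effective rate = number of patients with effective analgesia/total number of cases". Plans for assessment {18a} repeats that single outcome. Adverse reactions are not among the secondary outcomes in either section.
- **Sample size {14}:** built on "NRS score (at rest) ≤ 3 points during operation and within 48 h after the operation was defined as effective", with this assumption: "Assuming that the effective rate was 90% in the nalbuphine group and 90% in the morphine group". The margin is 10 percentage points, with one-sided alpha 0.025 and power 0.8.
- **Statistical analysis method (under Data management {19}):** the only success rule is a lower 95% confidence limit above −10% for the difference in response rates. For safety it says: "The incidence of adverse reactions will be calculated, their frequency and proportion were systematically listed, and the percentage calculated". Methods for additional analyses {20b} repeats the same descriptive plan.
- **Adverse event reporting and harms {22}:** the heading calls these the primary safety indicators. The list is open-ended and longer, running on to "urinary retention, hypoxemia, respiratory depression, drowsiness, delirium, and myoclonus are recorded".

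**The concern.** An endpoint with primary status should have a defined variable, a comparison between arms and a rule for reading the result. Here the status is given in the abstract and echoed in the harms section, but the Outcomes section drops it and the analysis section attaches no comparison to it.

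This matters because Objectives {7} sets out to compare both efficacy and safety, and the Background presents nalbuphine as similar to morphine in potency with fewer side effects. Sample size {14} assumes equal effective rates, so under the plan's own assumption an advantage would have to appear in the adverse reactions. That is the comparison with no estimate or test attached. If the plan is followed as written, the report will show two columns of percentages for a declared primary endpoint. Readers will have to judge the difference without an interval.

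**Working it through.** **1. What the stated sample size covers.** Inputs from Sample size {14}: 90% in each arm, margin 0.10, one-sided alpha 0.025, power 0.80, ratio 1:1.

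n per arm = [p1(1−p1) + p2(1−p2)] × (z0.975 + z0.80)² / margin² = (0.09 + 0.09) × (1.960 + 0.842)² / 0.10² = 141.28, rounded up to 142.

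Total 284; 284 / 0.9 = 315.6, rounded up to 316. Power at 142 per arm is 80.2%. The plan's figures reproduce exactly from the effective rate alone, so they contain no allowance for a second primary.

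**2. The two endpoints side by side.**

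| Element | Effective rate | Adverse reactions |
|---|---|---|
| Primary in the abstract | yes | yes |
| Listed in Outcomes {12} | main outcome | absent |
| Assumed rates, margin or difference | 90% v 90%, 10 points | none |
| Alpha | one-sided 0.025 | none assigned |
| Between-arm estimate or test | difference with 95% CI, chi-square family | none |
| Success rule | lower limit above −10% | none |

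The same analysis paragraph names between-arm tests for NRS scores, physician and nurse satisfaction, duration of surgery, hospital stay, daily dose and uninterrupted completion.

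**3. What 142 per arm could show for adverse reactions.** The documents give no reaction rates, so the morphine incidences below are assumptions. Two-sided alpha is 0.05, with pooled variance under the null and unpooled variance under the alternative:

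power = Φ{ [d − 1.96 × √(2p̄(1−p̄)/n)] / √[(p1(1−p1) + p2(1−p2))/n] }

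Example, 30% v 20%: √(2 × 0.25 × 0.75/142) = 0.0514 and √((0.21 + 0.16)/142) = 0.0510. Then (0.10 − 1.96 × 0.0514)/0.0510 ≈ −0.01, and power is 49%.

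| Assumed morphine incidence | Power, 10-point reduction | n per arm for 80% | Power, 15-point reduction | n per arm for 80% |
|---|---|---|---|---|
| 20% | 66% | 199 | 97% | 76 |
| 30% | 49% | 294 | 86% | 121 |
| 40% | 42% | 356 | 77% | 152 |
| 50% | 40% | 388 | 73% | 170 |
| 60% | 40% | 388 | 72% | 173 |

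A 10-point reduction is below 80% power throughout. A 15-point reduction is above 80% only at the two lower incidences.

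**The case against.** The strongest reply is that the document can be read as having one primary efficacy endpoint and one primary safety indicator, with confirmatory status for efficacy only. The harms heading and the phrase about primary efficacy indicators in the analysis section both fit that reading. The only success rule given is non-inferiority of the effective rate, and a test or interval for adverse reactions could sit in an analysis plan that is not shown.

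Much of this stands. The absence of a safety test would not by itself be a finding in a condensed article. What remains is that the abstract gives both endpoints the same status, Outcomes {12} does not, and the article specifies tests for lesser endpoints while giving this one only counts. The text never says that the safety primary is descriptive.

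A reader might also draw stronger conclusions that the documents do not support:

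- **Inflated false-positive risk.** Six tests at 5% would give 1 − 0.95⁶ = 26.5%, and eleven would give 1 − 0.95¹¹ = 43.1%, assuming independence. The plan contains no such tests, and these reactions share one drug exposure.
- **True power of about 40% instead of 80%.** With 30% v 20%, 0.80 × 0.494 = 0.395. This needs a rule that both endpoints must succeed, which the plan does not state, as well as independence and one chosen pair of rates. Sample size {14} claims 80% for the effective rate only, and that claim is right.
- **No definition of which reactions count.** The abstract and both arm descriptions agree on six. The longer list in {22} is introduced as examples to be recorded and reads as the collection list. It also counts nausea and vomiting separately, so its eleven items do not compare directly with six.

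**Conclusion.** The contradiction is in the text and should be corrected. Adverse-reaction incidence is declared primary in the abstract and labelled primary in the harms section, but it is not an outcome in {12} and has no share in the sample size, alpha or success rule. Its analysis has no between-arm comparison. As written, the plan cannot support a conclusion on that endpoint or on the safety half of its objective.

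The effective-rate primary, its margin and the 142 per arm (316 in total) are unaffected. How informative the trial would be on reactions depends on rates the documents do not give. Under the assumed incidences of 20% to 60%, power is about 40% to 66% for a 10-point reduction and about 72% to 97% for a 15-point reduction. These ranges illustrate what 142 per arm could detect; they are not an error in the stated power.

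**What to change.** - State in the abstract, Outcomes {12} and the harms section {22} that the analgesic effective rate is the sole confirmatory primary endpoint and the basis of the sample size, and that adverse-reaction incidence is a key secondary (main safety) endpoint.
- Define that endpoint as the proportion of patients with at least one of the six reactions named in the abstract and in {11a}, within 48 h. State which grade of hypoxemia counts as an event; the grading under Observation of AEs is headed 1 to 4 but defined as 0 to 3, so the two must first be reconciled.
- Count events regardless of causal attribution, because Who will be blinded {17a} blinds only patients.
- Report the between-arm risk difference with 95% CI. Make any formal test only after non-inferiority is shown. Report single reactions descriptively, with confidence intervals.
- Keep the wider list in {22}, including respiratory depression, for collection and reporting, and say there that it is wider than the endpoint list.

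Cost: enrolment began in October 2021, so changing the status of a published primary endpoint is a protocol amendment that needs ethics approval. It adds one analysis. It needs no new data and does not change N.

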**Discussion:**

This study, to the best of our knowledge, is the first randomized controlled trial of nalbuphine patient-controlled analgesia in ablation surgery.

**Trial registration:**

U.S. Clinical Trials Network Registration No.: NCT05073744. Registered on 11 October, 2021.

**Supplementary Information:**

The online version contains supplementary material available at 10.1186/s13063-022-06825-5.

## Administrative information

Note: the numbers in curly brackets in this protocol refer to SPIRIT checklist item numbers. The order of the items has been modified to group similar items (see http://www.equator-network.org/reporting-guidelines/spirit-2013-statement-defining-standard-protocol-items-for-clinical-trials/).

## Introduction

### Background and rationale {6a}

Malignant tumors have become one of the major public health problems that critically threaten the health of the Chinese population. According to the latest statistical data, malignant tumors are the leading cause of death, accounting for 23.91% of all-cause mortality in residents of China [1]. The morbidity and mortality of malignant tumors have shown a constant rise in the past decade [2]. The World Health Organization/International Agency for Research on Cancer (WHO/IARC) released the 2020 Global Cancer Report [3], which states that there were 18.1 million new cancer cases and approximately 9.55 million deaths worldwide in 2018. The latest statistical report by the China National Cancer Center [4] declared that there were 3.929 million new cancer cases and 2.338 million cancer deaths in 2015. The most frequent cancer types included lung, gastric, colorectal, liver, breast, esophageal, and gastrointestinal cancer [5]. In recent years, biomedical discipline has continuously evolved to develop new technologies and methods, and interventional tumor therapy has grown into a comprehensive treatment option for tumor patients owing to its high efficiency, safety, minimally invasive nature, and targetability [6].

Tumor ablation is a common non-vascular interventional tumor therapy and has been recommended by several guidelines for treating diverse solid tumors, for example, liver cancer and lung cancer [7–14]. The guidelines for the treatment of liver cancer recommend radiofrequency, cryotherapy, absolute alcohol injection, and microwave ablation (MWA) as local therapies [8]. These tumor ablation techniques are guided by imaging equipment (such as CT and ultrasound) and puncture needles into the tumor. Acting on the tumor tissue by physical or chemical means makes the tumor tissue necrotic and inactive, so as to achieve the purpose of controlling and eliminating the tumor. In 2018, the number of MWA procedures performed in China has increased to 100,000, accounting for 48% of the global number of these procedures. With continuous progress and development of ablation technology as well as the gradual increase of clinical high-grade evidence, tumor ablation is expected to become one of the preferred methods for treating early-stage solid tumors and an alternative for surgery [15].

With the popularization of interventional therapy for cancer, pain caused by the therapy has become the major problem that medical staff and patients need to consider. The degree and duration of pain vary according to interventional radiology technique; additionally, there are great individual differences, such as radiofrequency ablation being accompanied by burning and tingling sensations in the viscera and skin [16]. A study on ablation therapy in patients with hepatocellular carcinoma [17] indicated that 70.6% and 25% of patients had an intraoperative pain score > 4 and > 8 points, respectively, with a higher pain level in patients with multiple ablations than in those with one ablation (6.76 ± 1.96 versus 5.28 ± 2.48). The sedation/analgesia guidelines for interventional diagnosis and treatment published by the European Society of Anesthesiology [18], the American Society of Anesthesiologists [19], the American Association of Interventional Pain Physicians [20], and the European Society of Cardiovascular and Interventional Radiology [21] recommend opioids such as morphine for analgesia before, during and/or after interventional surgery, to ensure good patient experience.

Opioids are the drugs of choice for the clinical treatment of pain, and morphine, being a classic opioid analgesic, is widely used in clinical practice [15, 22, 23]. Morphine is an opioid receptor agonist, has low lipid solubility and strong analgesic efficacy, and is mainly bio-transformed in the liver with a half-life of 2–4 h [24]. Although morphine has a positive analgesic effect, many patients cannot tolerate it and switch to other opioids due to adverse effects such as respiratory and circulatory depression [25–27], nausea and vomiting [28], and addiction [29].

Nalbuphine is a morphinan semisynthetic agonist-antagonist opioid, which exerts pharmacological effects mainly by activating kappa (κ)-receptors and antagonizing mu (μ)-receptors. It has a strong analgesic effect, and can antagonize nausea and vomiting caused by some μ receptors [30]. With intravenous administration, the onset of action is 2–3 min with a peak at 30 min, half-life of approximately 5 h, and duration of action of approximately 3–6 h. The analgesic potency is similar to that of morphine, but it has fewer side effects and higher safety. Compared with morphine, incidence of skin itching, nausea, vomiting, and respiratory depression were significantly reduced [31]. Nalbuphine is mainly used for the treatment of conditions accompanying moderate to severe pain [32], including burns, multiple trauma, orthopedic injuries, and gynecological and intra-abdominal diseases [33, 34]; it can be infused intravenously, epidurally, and subcutaneously through mechanical or microcomputer analgesic pumps.

Patient-controlled analgesia (PCA) is a pain management technique in which medical staff pre-sets the dose of analgesic drugs according to the patient's pain level and physical condition, which enables patient self-management. It is clinically applied to various types of pain, such as postoperative pain, pain due to labor, cancer, burn, and trauma, and acute pain [35–38]. Compared with traditional intravenous and subcutaneous analgesics, PCA has certain advantages: (1) lower peak concentration of the analgesic drug during analgesic treatment, minor fluctuation of plasma concentration, low incidence of respiratory depression, and reduced side effects of excessive sedation; (2) better pain control; (3) it can overcome the individual differences related to the kinetics and pharmacodynamics of analgesics through on-demand administration; (4) reduced patient wait time for medical staff to assist with pain; (5) reduced incidence of postoperative complications; (6) improved satisfaction rate of patients and their families with medical quality; and (7) reduced workload on medical staff [39].

Although relevant guideline consensus and clinical studies recommend the use of opioids for analgesia treatment in interventional surgery through intravenous, subcutaneous, and intramuscular injections, PCA, and other means, no study has evaluated the use of nalbuphine PCA for analgesia in ablation surgery so far; additionally, its efficacy and safety have not yet been demonstrated in a large number of clinical trials in China.

Therefore, a randomized controlled study was planned to compare the efficacy and safety of nalbuphine patient-controlled intravenous analgesia (PCIA) with morphine PCIA for perioperative analgesia in ablation surgery including patients with different types of cancer and ablation surgery, surgical conditions, and analgesic methods in hospitals at all levels to provide a reference and suggestions for clinically important standardized perioperative analgesia in ablation surgery.

